## Intervention delivery, training and supervision

Each research site will have a control and two separate intervention teams trained to deliver either the MET or SBNT intervention. For example, in Newcastle (the smallest drug and alcohol team) as part of the preparatory work for the application, it has been agreed that the existing team of six people will be split into three teams of two workers each. Two workers will be trained by the research team to use MET, two will be trained to use SBNT and two workers (control) will have no additional training. Provision will be made for leave. The MET and the SBNT sub teams will have separate external intervention-specific supervision delivered by the research team. A similar method to minimise contamination has been used by the team as part of the HTA funded Y-SBNT study.[^36^](#_ENREF_36) Possible residual contamination of co-workers residing in the same premises, will be explored within the process evaluation before full trial.

We aim to offer 6 sessions of SBNT or MET, with each session lasting 50 mins. In both intervention arms, sessions will be offered weekly to fortnightly, with a maximum period of 12 weeks. The rationale for this number of sessions stems from learning from the UKATT trial and pilot work using SBNT with young people referred to child and adolescent mental health services. The final number of sessions offered will be finalised as part of the formative research. We will assess the number of sessions offered and actually attended by LAC to determine the appropriate number of sessions in a definitive trial. We will incorporate to feedback on duration, content, and location of sessions in the final specification of our intervention to ensure the intervention is acceptable to LAC and staff and can be delivered at scale by existing services.

## Known Risks

Based on previous experience we do not anticipate any significant harm or consequences to result from the interventions. All relevant risk assessments and responses to risk protocols from the participating services will be adhered to. In terms of social harms, the particular focus of the social intervention is on positive support, using a range of strategies to identify those people in the young person’s social environment that could offer this type of positive support. If the interventions uncover unmet medical or psychological need, onward referral to appropriate services will be initiated.

## Concomitant Medications & Therapies

Young people already in active treatment with drug and alcohol services will be excluded from the study as outlined in Section 5.1.2 and will be noted in the trial flow diagrams.

# ASSESSMENT OF COMPLIANCE/ PROCESS EVALUATION

The process evaluation aims to understand and document the key lessons learned from implementing SOLID (both the interventions and the trial processes) and to evaluate factors needed to deliver the intervention at scale. It will use a mixed methods approach (collecting both quantitative and qualitative data), based on the framework outlined by Steckler and Linnan (2002)[^62^](#_ENREF_62) but enhanced to include an emphasis on the mechanism of change at the level of the service provider (implementation, embedding and integration of the interventions – informed by Normalisation Process Theory) and behaviour change at the level of the individual young person (LAC).

The evaluation will also specifically explore contamination through 1:1 interviews with LAC and the Drug and alcohol worker. Core components of the evaluation are presented in Table 3 on page 45.

We will use Carroll’s (2007) definition of fidelity i.e. we will assess whether intervention sessions are delivered as planned in terms of content, frequency, duration and coverage [^63^](#_ENREF_63). These largely quantitative measures, derived from attendance records, will be supplemented by detailed assessment of audio-taped sessions and evidence from qualitative interviews and focus groups with Drug and Alcohol workers and managers. We propose to assess the quality of intervention delivery (treatment fidelity) by applying a validated process rating scale (UKATT PRS)[^64^](#_ENREF_64), developed in the UKATT trial. All sessions will be audio recorded and a 20% random sample of SBNT and MET sessions will be analysed ensuring we sample early, mid and late sessions of both interventions. UKATT PRS specifically covers MET and SBNT and assesses items including commitment, optimism, collaboration and interpersonal focus which help determine if the LAC are actively engaged in the intervention sessions. To make this assessment, the two research associates will independently rate the sampled audio-taped intervention sessions covering the 1 to 6 sessions for MET and SBNT.

Interview schedules for staff will be constructed to highlight the 4 core concepts of Normalisation Process Theory [^65^](#_ENREF_65):

1. *Coherence:* a shared understanding of the work **(do the workers understand the aims and the logic behind the intervention?)**
2. *Cognitive participation*: a shared agreement and engagement with the techniques of the work **(do the workers ‘buy into’ and ‘own’ the aims and logic behind the intervention and the ways in which it is being implemented?)**
3. *Collective action:* agreement with the organisation of the work **(what do the workers and managers do in practice to make the intervention work in their setting for themselves and the client group?)**
4. *Reflexive monitoring:* assessment and monitoring of the work **(are the workers engaged enough to be able to suggest improvements to the logic or practice of the intervention?)**.

This theory driven process evaluation will allow us to understand the extent to which staff understand the principles and core components of the interventions, value and believe in them, make adaptations to their usual work plan to ensure the interventions are delivered successfully and reflect on ways which they can improve delivery of the service. The analysis will inform our understanding of the mechanism of change from a practitioner perspective and consider key barriers to successful delivery and integration of the interventions at the level of the system.

Along with mechanism of change from the perspective of the service provider, we will collect qualitative data from LAC and their carers to understand how the interventions have affected the LAC themselves and how they would recommend changing the interventions to make them more effective. We will specifically probe around the proposed determinants of change illustrated in the BDI theory of change models (Figures 1 and 2, on pages 26 and 31 respectively). These data will allow us to refine these models.

## Data Collection

As highlighted in Table 3, on page 45, we will collect both quantitative and qualitative data to assess each of the process evaluation questions. Quantitative data will include a review of attendance records. Consent for access to participant records will be taken during initial consenting for the trial along with permission to potentially be contacted as part of the process evaluation. Qualitative data will be collected from a purposive sample of LAC (aiming for a maximum diversity sample – sampling criteria will be gender, placement type, study arm and age), their carers, social workers and Drug and alcohol workers. Data collection will continue until saturation; however as a minimum we will carry out 20 qualitative interviews with LAC, 20 interviews with carers, fifteen interviews with Drug and alcohol workers and two focus groups one with social workers and one with members from the drug and alcohol teams. Qualitative contacts will be preceded by informed consent. Interviews will take place within 3 months of intervention delivery. As outlined, all MET and SBNT sessions will be recorded and a 20% random sample will be independently rated by two researchers using the UKATT PRS. The UKATT PRS will be trialled and adapted as part of the pre-pilot feasibility trials in the formative research phase. Consent for this part of the study again will be taken at trial enrolment, however, the Drug and alcohol worker will make it clear that the young person can refuse to audiotaping of their session if they wish – this will not affect their participation in the study as a whole.

## Data Analysis

Qualitative data will be analysed thematically based on the constant comparison approach.

Where more than one source of data is collected for a given research question, findings will be triangulated e.g. for fidelity, we will explore content of sessions and probe on key aspects of input (qualitative interview data from LAC; log book entry plus focus group data from Drug and alcohol workers), frequency and duration (questionnaire data to be completed by Drug and alcohol services and verified by the researcher against service records) and coverage (assessment of the number of sessions offered and received, along with equity of intervention delivery by age, placement type and geographic coverage). Triangulation enhances the validity of conclusions by exploring the convergence, complementarity and dissonance of results on related research questions obtained from different methodological approaches, sources, theoretical perspectives, or researchers.[^66^](#_ENREF_66)

In this case we will use methodological triangulation, data triangulation and investigator triangulation. The range of both quantitative and qualitative data will be brought together using a ‘triangulation protocol’. [^67^](#_ENREF_67)^,^ [^68^](#_ENREF_68)This involves identifying themes or threads from each data source and method, and then sorting these into similar categories. These are then ‘convergence coded’ to identify where there is agreement, silence and dissonance in terms of data from different sources and methods.

Table 3: Specification of the Process Evaluation

| Process evaluation component | Key research questions | Additional information | Data source |
| --- | --- | --- | --- |
| **Recruitment and reach** | i. Has SOLID been able to recruit LAC (numbers screened, numbers screened positive, number consenting to participate in the study)? | Equity in terms of by age, placement type and geography. | Drug and alcohol services records, trial screening logs, consent forms, records of who was retained, and records of when and if possible why participants dropped out of the study. |
|  | ii. Was recruitment equitable across demographic groups |  |  |
| **Dose delivered** | iii. Were intervention sessions offered to young people?  iv. What proportion of these sessions were completed? |  |  |
| **Fidelity** | v. Were the interventions delivered as planned? | Fidelity defined by Carroll (2007) i.e. content, frequency, duration and coverage. | Content: Qualitative interview data from LAC;  Log book entry plus focus group data from Drug and alcohol workers. |
|  |  |  | Frequency and duration: questionnaire data to be completed by Drug and alcohol services and verified by the researcher against service records |
|  |  |  | Coverage: Drug and alcohol service records number of sessions offered and received. |
|  | vi. To what extent have the new interventions been integrated into routine practices? | Guides developed based on normalisation theory to probe: coherence, cognitive participation, collective action and reflexive monitoring (May and Finch 2009). | Qualitative focus group discussions plus interviews with Drug and alcohol workers. |
| **Quality (treatment fidelity)** | vii. Were the interventions delivered with quality? | UKATT Process rating Scale: 7 items for MET and 8 items for SBNT to measure quality (treatment fidelity) | Researcher analysis of audio recording of a random 20% subsample of intervention sessions using UKATT process rating scale for MET and SBNT. |
| **Dose received/ acceptability** | vii. Was the intervention acceptable to LAC? If not why not? |  | Qualitative interviews with LAC |
| **Retention in the trial** | viii. What was the proportion of young people recruited into the trial who were retained till 12 month follow up and what measures can increase trial retention? |  | Trial records of recruitment and retention.  Qualitative interview data from LAC |
| **Contamination** | ix. To what extent did Drug and alcohol workers know about and were influenced by SBNT/ MET also being undertaken in their hub? |  | Qualitative interviews and focus group discussions with Drug and alcohol workers and managers. |
|  | ix. To what extent did LAC know about and were influenced by SBNT/ MET interventions being offered to other LAC that they knew? |  | Qualitative interviews and focus group discussions with Drug and alcohol workers and managers. |
| **Mechanism of change** | x. What were the facilitators and barriers to integration of the interventions into the Drug and alcohol service? | Normalisation theory components coherence, cognitive participation, collective action and reflexive monitoring (May and Finch 2009). | Qualitative interviews and focus group discussions with Drug and alcohol workers and managers. |
|  | xi. Did the interventions make a difference to the lives of LAC and did they alter their behaviour? Are the BDI models appropriate for the mechanism of change? |  | Qualitative interviews LAC and their carers. |

# Study Timeline

Figure 5 Study Timeline SOLID Project Gantt chart

|  | Months | 1- 3 | 4 - 6 | 7- 9 | 10 -12 | 13- 15 | 16- 18 | 19 -21 | 22 -24 |
| --- | --- | --- | --- | --- | --- | --- | --- | --- | --- |
| Phase 1 Formative study | Qualitative data collection and analysis |  |  |  |  |  |  |  |  |
|  | Pre-pilot feasibility trials |  |  |  |  |  |  |  |  |
|  | Intervention finalisation workshops |  |  |  |  |  |  |  |  |
|  | On Line Survey of LAC leads |  |  |  |  |  |  |  |  |
|  | Formative research report |  |  |  |  |  |  |  |  |
| Phase 2 Pilot RCT | Recruitment |  |  |  |  |  |  |  |  |
|  | Intervention delivery |  |  |  |  |  |  |  |  |
|  | Process evaluation |  |  |  |  |  |  |  |  |
|  | Economic tool development and VOI analysis |  |  |  |  |  |  |  |  |
|  | Follow up data collection |  |  |  |  |  |  |  |  |
|  | Analysis/writing up/dissemination |  |  |  |  |  |  |  |  |
| Study steering Committee (SSC) meetings | |  |  |  |  |  |  |  |  |
| Dissemination events | |  |  |  |  |  |  |  |  |

# SAFETY REPORTING

## Definitions

| Term | Definition |
| --- | --- |
| Adverse Event (AE) | Any untoward medical occurrence in a participant, including occurrences which are not necessarily caused by or related to the intervention under study. |
| Adverse Reaction (AR) | An untoward or unintended response in a participant which is related to the intervention under study i.e. that a causal relationship between the trial intervention and an AE is at least a reasonable possibility and the relationship cannot be ruled out.  All cases judged by either the reporting medically qualified professional or the Sponsor as having a reasonable suspected causal relationship to the trial intervention qualify as adverse reactions. |
| Serious Adverse Event (SAE) | A serious adverse event is any untoward medical occurrence that:   - Results in death - Is life-threatening* - Requires inpatient hospitalisation or prolongation of existing hospitalisation - Results in persistent or significant disability/incapacity - Other important medical events that jeopardise the participant or require intervention to prevent one of the above consequences   * - life-threatening refers to an event in which the participant was at immediate risk of death at the time of the event; it does not refer to an event which hypothetically might have caused death if it were more severe. |
| Serious Adverse Reaction (SAR) | An adverse event that is both serious and, in the opinion of the reporting Investigator, believed with reasonable probability to be due to the trial intervention, based upon the information provided. |
| Unexpected Serious Adverse Reaction (USAR) | A serious adverse reaction, the nature and severity of which is not consistent with the known information about the intervention under study. |

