# RATIONALE

Although the risk of substance misuse in LAC is well documented, service provision for this group is poor, with only 41% of those young people with substance use problems receiving help.[^31^](#_ENREF_31) Given the vulnerability to early onset substance use within LAC populations, secondary prevention interventions, which target young people who are already using substances may be more effective, cost effective, and salient to the individuals receiving it than universal, primary prevention approaches.

NICE guidelines recommend multiple sessions of motivational interviewing or family based support or group based behavioural therapy over 1 to 2 years to reduce substance use in high risk young people.[^11^](#_ENREF_11) Due to the complexity and length of these interventions they are not feasible to be delivered at scale. The current study will adapt and evaluate the pilot feasibility of two alternative evidence based counselling interventions: Motivational Enhancement Therapy (MET) – a concentrated form of MI developed within the NIH MATCH study;[^32^](#_ENREF_32) and Social Behavioural Network Therapy (SBNT) – an approach drawing from family and social interventions in substance use.[^33^](#_ENREF_33)^,^ [^34^](#_ENREF_34) Both interventions involve counselling but focus on different behaviour change pathways (illustrated in Figures 1 and 2), with internal thoughts and views shaping the decisional-balance in MET compared with external, social influences in SBNT.

For many LAC it is the experience of abuse or neglect from within their families that has led them to Local Authority care and may account for the high rates of psychiatric morbidity in this population.[^20^](#_ENREF_20) The absence of a supportive family unit has been associated with increased rates of substance misuse in young people.[^35^](#_ENREF_35) SBNT has been designed to mobilise and develop support networks which are wider than just biological family and include peers; it has been found to be effective in reducing substance misuse in adults when delivered through routine services.[^36^](#_ENREF_36) Interventions based on SBNT have the potential to address this central vulnerability within a LAC population. Details of the intervention packages are given in Section 6.

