## Recording and Reporting AEs and SAEs

All AEs and SAEs occurring from the time of randomisation in the Pilot RCT until follow up is completed (12 months post enrolment) must be reported. Depending on the nature of the event, the reporting procedures below should be followed. Any questions concerning adverse event reporting should be directed to the Chief Investigator or the Study Coordinator (Research Associate) in the first instance.

**Adverse Event (AEs):** All non-serious adverse events (as defined in section 9.1 above and including non-serious adverse reactions) during study participation must be recorded on an adverse event/harms case report form and sent to the Study Coordinator within 2 weeks of the event. Severity of AEs will be graded on a three-point scale (mild, moderate or severe). The Study Coordinator will enter the data onto the study database. In addition, the Study Coordinator will contact the LAC team manager monthly to ensure no adverse events are missed.

Expected AEs include the following:

- Severe drug and alcohol use
- Mental health difficulties
- Self-harm and suicidal ideation

**Serious Adverse Event (SAEs):** All SAEs (as defined in section 9.1 above and including serious adverse reactions) during study participation must be reported to the Chief Investigator within 24 hours of the site becoming aware of the event. The initial report should ideally be made by completing the study SAE form and sending via the fax number listed on page 64 of the protocol. Alternatively, if this is not possible, the initial report may be made by telephone to the number listed on page 64 of the protocol. In the case of incomplete information at the time of initial reporting, all appropriate information should be provided as follow-up as soon as this becomes available. Relationship of the SAE to study procedures will be assessed by the Chief Investigator, as will the expected or unexpected nature of the SAE.

As the study deals with a vulnerable population, expected SAEs include those related to the following which result in hospitalisation:

- Severe drug and alcohol use
- Mental health difficulties
- Self-harm and suicidal ideation

SAEs exclude:

- any pre-planned hospitalisations (e.g. elective surgery) not associated with clinical deterioration
- routine treatment or monitoring of the studied indication, not associated with any deterioration in condition

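### Safety reporting is limited to medical occurrences, so the social harms raised under Known Risks are captured only indirectly and not as safety events

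*Protocol*

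**What the plan says.** Section 9.1 of the Protocol defines an adverse event as "Any untoward medical occurrence in a participant, including occurrences which are not necessarily caused by or related to the intervention under study". The serious category has the same root: "A serious adverse event is any untoward medical occurrence that" meets one of the listed seriousness criteria. The adverse reaction definition opens more widely, with "An untoward or unintended response in a participant which is related to the intervention under study", but then explains itself as a causal link between the intervention and an adverse event, which leads back to the medical definition.

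Section 9.2 takes its scope from section 9.1. Non-serious events so defined "must be recorded on an adverse event/harms case report form and sent to the Study Coordinator within 2 weeks of the event". As a check, "the Study Coordinator will contact the LAC team manager monthly to ensure no adverse events are missed". The expected events listed, serious and non-serious, concern substance use, mental health, and self-harm or suicidal thoughts.

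Section 6.3 (Known Risks) says that "we do not anticipate any significant harm or consequences to result from the interventions". It then takes up a different kind of harm: "In terms of social harms, the particular focus of the social intervention is on positive support". It gives no route for recording a social harm if one occurs.

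**The concern.** SBNT and MET differ mainly in their use of other people. Table 2 in section 6.1 has the SBNT therapist always trying to bring in significant others, whereas in MET they are peripheral. Section 6.1 adds that the SBNT network may include peers and wider family. Section 2 describes the population: "For many LAC it is the experience of abuse or neglect from within their families that has led them to Local Authority care". Section 5.2.3 accepts that contact with a parent can itself put a young person at risk.

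If the two active arms differ in harm, network contact is a plausible place for it. Events of that kind, such as a safeguarding incident or conflict with a network member, need not be medical. The pilot is to inform whether one intervention, or a combined version, goes forward (sections 2 and 3.2). A harm specific to one arm should be visible to that decision in the same form for every participant.

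**Working it through.** The point rests on no figure in the plan, so the check is a comparison of the text.

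**Step 1. Does a non-medical harm meet a reporting definition?** Take a young person who, after a session involving a network member, is the subject of a safeguarding incident or is in serious conflict with that person, with no injury and no change in mental health.

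- Adverse event: no, because it is not a medical occurrence.
- Serious adverse event: no, for the same reason. The catch-all criterion also speaks of medical events.
- Adverse reaction: the opening words would admit it. The explanatory clause requires an adverse event, so on a literal reading it is out.
- Expected-event lists: they contain no social event.
- Monthly check with the LAC team manager: its stated purpose is to find missed adverse events, so it inherits the same definition.

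The exclusion follows from a stated rule, not from silence.

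**Step 2. What other routes exist?**

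| Route (Protocol section) | Coverage | What it could show | What it lacks |
|---|---|---|---|
| 12-month questionnaires (3.5, 5.5, Table 1) | All arms, one time point | Placement stability, antisocial and criminal behaviour, sexual regret and unprotected sex, use of health and social services | No relatedness assessment; no baseline values scheduled; none is described as asking about harm by, or conflict with, network members |
| Linked social services records (3.5, 12.1) | Those who consent to linkage | Longer-term placement stability, without depending on questionnaire completion | Placement only; no relatedness assessment |
| Process-evaluation interviews (7, 7.1, Table 3) | Purposive sample, within 3 months of delivery | How the young person was affected, as told by them and their carer | Not all participants; no systematic harms item |
| Session recordings (7, 7.1) | 20% random sample rated, where recording is not refused | Treatment fidelity | Rated on a process scale, not for harms |

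**Step 3. How far do the interviews reach?** The stated minimum is 20 young people. With the planned 150 recruited, 20 / 150 = 13%. This assumes full recruitment and the minimum number of interviews; sampling to saturation could raise it. Carer interviews (also at least 20) add a second view, partly of the same young people.

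**Step 4. Is by-arm information available?** Section 10.2.2 tabulates outcome data for each arm, so the 12-month measures will be comparable between arms. Section 9.4 has the oversight committee review safety data for trends. A non-medical harm outside the adverse event definition does not enter those safety data.

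**Step 5. Could a statistical analysis plan repair this?** It can specify tables. It cannot tabulate events that the protocol did not require anyone to collect.

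**The case against.** The strongest reply is that the protocol is less narrow in practice than its definition. The form is titled for adverse events and harms. The expected events include a behaviour (severe substance use), and mental health difficulties would take in the psychological consequences of a social harm. Section 6.3 applies the services' own risk assessments and risk protocols. Section 9.6 covers immediate hazards to safety as well as health, and makes every member of the research team responsible for reporting. Section 5.8 asks for reasons for withdrawal. The interviews precede the choice of intervention and sample by study arm. Finally, section 6.3 does not promise to record social harms, so nothing promised is missing.

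Much of this stands. It shows that some social harms would probably come to light and that the form could already hold them. It does not give a recording rule: none of these routes yields a dated event with a relatedness assessment for every participant. The title of the form supports the change, since it suggests that wider capture was in mind.

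It is also true that the protocol describes no analysis of adverse events of any kind. A missing by-arm safety table is therefore not specific to social harms, may belong in an analysis plan that is not shown, and is not part of this point.

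**Conclusion.** The point holds in limited form. Sections 9.1 and 9.2 confine safety reporting to medical occurrences, while section 6.3 raises social harms and the SBNT–MET contrast turns on involving other people. Non-medical harms are captured only indirectly, and not as safety events with timing and relatedness in all arms. This rests on a literal reading of the definitions; sites might report more widely. It is a worthwhile and cheap improvement, not a flaw that undermines the pilot's feasibility aims.

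Three stronger readings are tempting and are not supported:

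- A reader might infer that the protocol names social harm as the relevant risk of SBNT. It does not. Section 6.3 anticipates no significant harm and mentions social harms in order to explain how the intervention's focus counters them.
- A reader might infer that such harms are never recorded or compared. Placement stability, antisocial and criminal behaviour and sexual behaviour are collected in all arms at 12 months, and outcome data are tabulated by arm.
- A reader might put the capture rate at zero, or say that placement data will be missing for the planned 30% lost to follow-up. The first turns a literal reading into a measurement. The second overlooks linkage to social services records, which does not depend on answering the questionnaire, although the protocol describes it for longer-term stability and does not say when that consent is taken.

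The documents give no rate of safeguarding incidents, network conflict or placement breakdown, so the number of events affected cannot be stated.

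**What to change.** Reconcile section 6.3 with sections 9.1 and 9.2 so that the protocol says whether and how non-medical harms are recorded. Specifically:

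1. Widen what is recorded on the existing adverse event/harms form to include non-medical (social) harms. Give examples, such as a safeguarding incident, conflict with or harm by a network member, and unplanned placement breakdown.
2. Apply the same relatedness assessment and dating as for other events.
3. Ask about these harms in the existing monthly contact with the LAC team manager, for participants in all arms. This matters for even ascertainment: Table 1 also places adverse event assessments at the intervention sessions, which control participants do not have.
4. Summarise these harms by arm alongside the placement-stability data, and include them in what the oversight committee reviews.

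This concerns recording only; it leaves safeguarding and clinical responses as they are. The cost is changed wording in the protocol and form, handled through the amendment process in section 14.9, with no new visit or instrument. The downside is more non-serious events to log, at a rate the documents do not give. A short definition of what counts would keep routine placement moves from swamping the form.
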